**FAI risk in sports specialists**			
20%	126	1388	1668
30%	61	193	1902
40%	38	81	240
50%	26	46	94

### Statistical plan

#### Primary analysis

As previously described, study groups will be defined at the completion of follow-up given participant activity levels may change over time. The proportion of subjects developing FAI in the sport specialist group versus non-sport specialist group will be compared using a logistic regression analysis with FAI as the dependent variable and will include the following independent variables: activity level (sport specialist versus non-sport specialist), body mass index (BMI), and sex. Results will be reported as odds ratios (OR) with 95% confidence intervals and associated *p*-values.

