### Study objectives

The primary research objective is to determine if sport specialization at the moderate-to-vigorous physical activity (MVPA) level [23–27] is associated with the development of both symptomatic and asymptomatic FAI (i.e. cam, pincer, or mixed-type) in adolescents (ages of 12–14 years) at 2 years post-enrollment determined via MRI.

The secondary research objectives are to determine if the presence of FAI is associated with changes in hip function and health-related quality of life (HRQL) at 2 years post-enrollment determined via the Hip Outcome Score (HOS) and Pediatric Quality of Life (PedsQL) questionnaires.

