### Participant selection

#### Eligibility criteria

The inclusion criteria are: 1) asymptomatic males and females between the ages of 12–14 years; 2) ability to speak, understand, and read the language of the clinical site; and 3) provision of informed child assent (if applicable) and parental consent.

The exclusion criteria mainly preclude known confounding factors that would impede the evaluation of the etiology of a hip deformity. These include: 1) hip is mature (i.e. closed physes) based on the baseline MRI scan; 2) hip complaints or pain in the hip; 3) previous trauma to the hip; 4) previous surgery on the hip; 5) significant medical co-morbidities (requiring daily assistance for activities of daily living); 6) history of or ongoing paediatric hip disease (Legg-Calve-Perthes; slipped capital femoral epiphysis, hip dysplasia); 7) participants that have contraindications and/or are unwilling to undergo an MRI (e.g. claustrophobia); 8) participants who will likely have problems, in the judgment of the investigator, with maintaining follow-up; and 9) any other reasons the investigator feels is relevant for excluding the subject (e.g. participant is planning to move in the next 2 years, unreliable access to transportation to attend follow-up visits, etc.).

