### Study outcomes

#### Primary outcome

The primary outcome is the incidence of radiographic FAI between groups at 2 years, as determined by the dedicated MRI of the hip (Table 2). We will identify both symptomatic and asymptomatic cases, where asymptomatic FAI can become symptomatic in young adulthood, and/or could be associated with idiopathic osteoarthritis later in life [41].

**Table 2 Tab2:** Criteria for defining FAI types

FAI type	Criteria
Cam	1. Alpha angle is > 55°; 2. Anterior head-neck offset < 10 mm; 3. Anterior head-neck offset ratio < 0.15 **Must meet 2/3 criteria to be considered cam impingement*
Pincer	1. Acetabular depth < 3 mm; 2. Lateral centre-edge angle > 39°; 3. Acetabular anteversion (in the upper third of the femoral head) < 0° **Must meet 2/3 criteria to be considered pincer impingement*
Mixed	**Must meet 2/3 criteria each for cam and pincer impingement (as per above) to be considered mixed impingement*

*FAI* Femoroacetabular impingement

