#### Outcome measures

Participants will complete the study questionnaires and undergo a physical examination (at baseline and 6, 12, 18, and 24 months) and MRI (at baseline and 24 months) of their dominant hip. Participants will sync their activity tracker data and send their activity log (at baseline and every 3 months until final follow-up at 2 years) (Table 3).

**Table 3 Tab3:** Schedule of events for the PREVIEW study

Data collection	Enrollment	3 M	6 M	9 M	12 M	15 M	18 M	21 M	24 M
Screening and informed consent	●								
Enrolment data (Demographics)	●								
Physical hip examination	●		●		●		●		●
MRI	●								●
Follow-up form	●		●		●		●		●
Activity tracker wear & synchronization	*	x	x	x	x	x	x	x	x
Activity log	*	x	x	x	x	x	x	x	x
Hip Outcome Score (HOS)	●		●		●		●		●
Pediatric QoL Inventory (PedsQL)	●		●		●		●		●
Adverse events			●		●		●		●

*M* months, *MRI* Magnetic Resonance Imaging, * = 1-week post-enrollment/baseline visit, x = 1-week prior to visit

The physical examination will include range of motion (ROM) measurements in all planes documented in the supine and prone positions by a blinded research assistant (using a goniometer), as well as response of provocative hip tests on both hips [44]. Symptomatic FAI in adolescents is typically characterized by anterior hip pain aggravated by flexion activities, decreased hip internal rotation, and a positive impingement sign [7]. We will define symptomatic FAI using the following criteria: 1) positive impingement with groin pain based on flexion, adduction, and internal rotation (FADIR) test, and 2) decreased ROM: internal rotation of the hip when compared to the contralateral side by 5 degrees [45, 46].

We will use a non-contrast three dimensional (3D)-volumetric interpolated breath-hold examination (VIBE) sequence MRI [47]. This protocol has been used to document FAI-related morphology and eliminates the use of intra-articular contrast injections. All MRI and physical examination information will be provided to an independent radiologist adjudicator to determine the incidence of cam, pincer, or mixed-type FAI according to the pre-specified criteria (Table 2). We will also document the change in cartilage volume, labral pathology, herniation pits on the femoral neck, and the extent of physeal closure as these variables may predict future hip osteoarthritis [44].

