### Sample size calculation

We have based our sample size calculation on our pilot study data (*N* = 53), where the primary outcome event rate (incidence of FAI) is 40% for the sport specialists at the MVPA level (group 1) and 15% for the non-sport specialists at all physical activity levels (group 2). These proportions very closely match prior cross-sectional research that evaluated the incidence of FAI among athletes [10]. Because we have looked at early data from the pilot study to inform our calculation, we have adjusted our type I error rate. To achieve 80% power for a two-sided test at alpha = 0.01, we will require a sample size of 81 in each exposure group (Table 4). Given that some participants’ activity levels may change during the course of the study (where they may change from sport specialist to non-specialist, or vice versa), we will increase the sample size by 10% to ensure we have at least 81 participants in each exposure group. We will also account for a 5% rate of ineligibility (due to a mature hip [closed physes] found on the baseline MRI) and a 10% loss to follow-up rate. Therefore, we require a total sample size of 200 participants. The pilot participants will be rolled into the definitive study.

**Table 4 Tab4:** Per group sample sizes. 80% power, alpha = 0.01, 2-sided testing

	FAI risk in non-sports specialists		
	5%	15%	25%

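### The protocol aims at new FAI, but no rule keeps FAI already visible on the baseline MRI out of the primary odds ratio

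*Protocol article*

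**What the plan says.** All references are to the Protocol article.

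- **Study objectives.** The question is whether sport specialization "is associated with the development of both symptomatic and asymptomatic FAI".
- **Eligibility criteria.** Participants are "asymptomatic males and females between the ages of 12–14 years". Of the nine exclusions, the only one that rests on a finding of the baseline scan is that the "hip is mature (i.e. closed physes) based on the baseline MRI scan". Cam or pincer morphology is not listed.
- **Primary outcome.** This section reads: "The primary outcome is the incidence of radiographic FAI between groups at 2 years, as determined by the dedicated MRI of the hip". The criteria in Table 2 define cam, pincer and mixed types by thresholds on a single scan and do not refer to change.
- **Outcome measures.** Each participant has an "MRI (at baseline and 24 months) of their dominant hip". MRI and examination data go to an independent radiologist adjudicator.
- **Primary analysis.** "The proportion of subjects developing FAI in the sport specialist group versus non-sport specialist group will be compared using a logistic regression analysis". The independent variables are "activity level (sport specialist versus non-sport specialist), body mass index (BMI), and sex".
- **Secondary outcomes and Secondary analyses.** The first section divides participants by whether FAI is present at 2 years. The second divides them by whether FAI arises during the 24 months.
- **Sample size calculation.** The rates are 40% and 15%, taken from the pilot. The text adds: "These proportions very closely match prior cross-sectional research that evaluated the incidence of FAI among athletes". Allowances are 10% for changed activity, 5% for mature hips and 10% for loss to follow-up.

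**The concern.** An incidence needs an at-risk set: participants without the condition at the start. The plan never defines one. Being free of symptoms does not supply it, because the protocol counts asymptomatic FAI as a case. A symptom-free child with cam or pincer morphology can therefore be enrolled, and nothing says how that child is counted at 24 months.

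The protocol's own Background makes this more than a theoretical case. It reports hip impingement in 14 to 17% of asymptomatic young adults and cam deformity in more than 50% of adolescent athletes in some sports. Recruitment reaches out to competitive clubs, and Table 1 describes specialists as training for more than 8 months a year. Specialists may thus enter with more FAI than non-specialists.

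If they do, an odds ratio from all participants can show an association when specialization during follow-up had no bearing on new FAI. If baseline FAI is equal in the groups, it can instead dilute a real association. In both cases the stated objective is not cleanly answered.

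**Working it through.** **1. The plan's own figure.** Inputs (Sample size calculation): p1 = 0.40, p2 = 0.15, two-sided alpha 0.01, power 80%. The pooled formula gives 74 per group, and with the continuity correction 81. The stated 81 reproduces, as do all 12 cells of Table 4. For the total, 2 × 81 × (1 + 0.10 + 0.05 + 0.10) = 202.5, against the stated 200. The point is not an arithmetic error.

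**2. What an all-participant analysis measures.** With baseline proportion b and incidence i among those free of FAI, and assuming that FAI once present stays present, the 24-month proportion is

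P = b + (1 − b) × i.

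**3. Unequal baseline FAI, no association with new FAI.** The documents give no baseline rates, so b and i are assumptions; i = 10% in both groups. Rejection is for an unadjusted two-proportion test without continuity correction, alpha 0.01, 81 per group.

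| Baseline FAI, specialists vs others | 24-month proportions | OR | Chance of rejection |
|---|---|---|---|
| 30% vs 5% | 37.0% vs 14.5% | 3.46 | about 77% |
| 20% vs 5% | 28.0% vs 14.5% | 2.29 | about 31% |
| 20% vs 10% | 28.0% vs 19.0% | 1.66 | about 11% |

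First row: 0.30 + 0.70 × 0.10 = 0.370; 0.05 + 0.95 × 0.10 = 0.145; OR = (0.370/0.630)/(0.145/0.855) = 3.46. The nominal rate is 1%.

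**4. Equal baseline FAI, real association.** Suppose that 40% and 15% are 24-month proportions and 10% of each group had FAI at entry. The incidences among those at risk are then (0.40 − 0.10)/0.90 = 33.3% and (0.15 − 0.10)/0.90 = 5.6%, with OR 8.5. The all-participant OR is (0.40/0.60)/(0.15/0.85) = 3.8.

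**5. Power after restriction, if 40% and 15% are true incidences.** The at-risk number per group is 81 × (1 − b). For the corrected column, the continuity correction is inverted: n_eff = n − 2/d + 1/(n d²), with d = 0.25.

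| Baseline FAI | At risk per group | Power, corrected | Power, uncorrected |
|---|---|---|---|
| 0% | 81 | 80% | 85% |
| 5% | 77.0 | 77% | 83% |
| 10% | 72.9 | 74% | 80% |
| 20% | 64.8 | 67% | 74% |

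Keeping 81 at risk needs 81/(1 − b) = 86, 90 or 102 per group at 5, 10 or 20%. Scaling the total, 200/(1 − b) = 211, 223 or 250.

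**6. Power after restriction, if 40% and 15% are 24-month proportions.** In the case of step 4 (33.3% vs 5.6%, 72.9 per group), power is about 94% corrected and 96% uncorrected. The cost of restriction therefore depends on what the pilot rates measure.

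**The case against.** The strongest reply is that the protocol says what it means. It speaks of development, of incidence and of participants developing FAI, and Secondary analyses refers to FAI that develops within follow-up. A hip positive at entry cannot meet that wording. The adjudicator receives all MRI information, scans are scheduled at both ends, and the at-risk set is a detail that an analysis plan, not shown here, might fix.

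Much of this stands. A reader might infer that the protocol specifies a prevalence analysis. It does not: new cases are plainly intended, and no sentence says that a child with FAI at entry counts as a 24-month case. A reader might also infer that the baseline MRI serves only to exclude closed physes. That is wrong too, since Outcome measures also calls for change in cartilage volume and sends MRI information to the adjudicator. Nor do the documents show that the planning rates are prevalences. They are attributed to the pilot, and the cross-sectional work is cited only as agreeing with them. Finally, the objective asks about association, so the plan should not be faulted for failing to prove causation.

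What does not stand is that the matter is mere missing detail. The exclusions, outcome, covariates and sample-size allowances are all listed explicitly, and together they leave baseline FAI in. Handing scans to an adjudicator is not a rule for counting hips that were positive at entry. Restricting the set later would change the primary population and its power.

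**Conclusion.** The concern holds as a missing rule with a contradiction attached. The intent is incidence, nothing in the specified analysis delivers it, and Secondary outcomes and Secondary analyses classify a baseline-positive child differently. It should be settled before the data are analysed.

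The size is unknown. The rejection rates of 11 to 77% in step 3 rest on assumed baseline rates and an assumed 10% incidence. They show what the design would permit, not what it will produce. The prevalences in the Background concern young adults, competitive athletes and adolescent athletes, not asymptomatic 12 to 14-year-olds with open physes, so they make baseline FAI plausible without giving its rate or its imbalance. If baseline FAI is rare, the effect is small.

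**What to change.** 1. Have the blinded adjudicator classify each baseline MRI by Table 2, and state that this is done.
2. Run the primary logistic model in participants without FAI at baseline, and state how participants with one FAI type at entry who later develop another are counted.
3. Keep the all-participant 24-month model as a sensitivity analysis.
4. Align Secondary outcomes with Secondary analyses on whether FAI means present at 2 years or newly developed.
5. Treat adjustment for baseline morphology (alpha angle, plus the pincer measures) as supportive. Morphology at entry may itself result from earlier training, so making it a mandatory primary covariate could remove part of the association of interest.
6. Restate power for the at-risk number, using the pilot's baseline scans to establish whether 40% and 15% are incidences or 24-month proportions.

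The cost is wording in the protocol and analysis plan and the reading of scans already scheduled. The downside is a smaller at-risk set, with the loss of power shown in steps 5 and 6. Restriction also does not remove other confounding in an observational comparison.

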#### Participant recruitment and screening

The study activities at each participating clinical site will be led by experienced hip surgeons and sports medicine physician researchers. However, because we are looking for healthy volunteers, participants might not be exclusively recruited from the co-investigators’ clinics. Instead, we will use several recruitment strategies that have proven successful in our pilot study. These include: 1) posting study flyers throughout each participating institution; 2) distributing study flyers to grades in the eligible age range at school boards in the regions of the recruiting institutions; and 3) having the co-investigators reach out to community coaches and competitive sport organizations and clubs, and presenting the study to the organizers, parents, and adolescent athletes. Potentially eligible subjects will be approached along with their parents/guardians for consent for participation.

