#### Subgroup/sensitivity analyses

To assess whether the magnitude of the effect of sport activity on the development of FAI is significantly different in males than in females, we will add an interaction term between sex and sport specialist versus non-sport specialist to the primary logistic regression model. We hypothesize that sport specialization will be more strongly associated with incidence of FAI in males than in females.

No interim analyses are planned. All tests will be 2-sided with α = 0.01. We will use SAS 9.4 (Cary, NC) to perform all analyses.

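### The primary logistic regression and the 81 per group assume independent children although recruitment runs partly through clubs and coaches; if several team-mates enrol, the standard error will be somewhat too small.

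*Protocol article*

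**What the plan says.** Protocol article, Participant recruitment and screening, lists three routes: flyers at the institutions, "distributing study flyers to grades in the eligible age range at school boards in the regions of the recruiting institutions", and "having the co-investigators reach out to community coaches and competitive sport organizations and clubs, and presenting the study to the organizers, parents, and adolescent athletes". Children are then approached and consented individually with a parent or guardian.

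Primary analysis fixes the comparison: FAI is "compared using a logistic regression analysis with FAI as the dependent variable and will include the following independent variables", namely activity group, BMI and sex. The article mentions no site, club or school term, no random effect and no robust variance.

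Sample size calculation takes an FAI incidence that "is 40% for the sport specialists at the MVPA level (group 1) and 15% for the non-sport specialists" and states: "To achieve 80% power for a two-sided test at alpha = 0.01, we will require a sample size of 81 in each exposure group". It adds allowances for group change, ineligibility and loss to follow-up, but none for clustering. Alpha is set at 0.01 because pilot data had been examined, and the Subgroup/sensitivity analyses section repeats: "All tests will be 2-sided with α = 0.01".

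**The concern.** Competitive clubs are a natural source of group 1, because Table 1 requires more than eight months a year in one sport to the exclusion of others. Team-mates share a sport, a coach and a training load. Where several enrol from one club, both their exposure and their FAI risk may be alike, and an ordinary logistic standard error is then too small.

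The group term does not necessarily absorb this. The Background ties hip conflict to movements found in particular sports, and the study takes in all sports, so clubs within group 1 can differ in risk. Adjusting for site or sport would not fully repair it either, since several clubs can share both.

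At stake are the width of the interval for the odds ratio and part of the protection that the stricter alpha was meant to give.

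**Working it through.** **1. The plan's own figure.** Inputs from Sample size calculation: 40% and 15%, two-sided alpha 0.01, 80% power; z values 2.576 and 0.842; mean proportion 0.275.

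- Uncorrected: n = [2.576·√(2·0.275·0.725) + 0.842·√(0.40·0.60 + 0.15·0.85)]² / 0.25² = 73.1.
- With continuity correction: n′ = (n/4)·[1 + √(1 + 4/(n·0.25))]² = 80.9, so 81.

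This reproduces the stated 81, and the same formula reproduces all 12 cells of Table 4. It treats children as independent.

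**2. Assumptions.** The article gives neither cluster size m nor ICC. I take an ICC of 0.05, with 0.02 and 0.10 as the range. At 40% incidence, 0.05 means a between-club standard deviation of √(0.05·0.24), about 11 percentage points.

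**3. Formulas.**

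- Exposure constant within cluster: DE = 1 + (m − 1)·ICC.
- Exposure mixed within cluster: DE = 1 + (m − 1)·ICC·(ICC of exposure).
- True alpha = 2[1 − Φ(2.576/√DE)].

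**4. Closed-form results for a nominal 0.01.**

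| Setting | DE | True alpha |
|---|---|---|
| Exposure unrelated to cluster | 1.00 | 0.010 |
| m = 2, constant exposure, ICC 0.05 | 1.05 | 0.012 |
| m = 5, exposure ICC 0.25, ICC 0.05 | 1.05 | 0.012 |
| m = 10, exposure ICC 0.25, ICC 0.05 | 1.11 | 0.015 |
| m = 5, constant exposure, ICC 0.05 | 1.20 | 0.019 |
| m = 10, constant exposure, ICC 0.02 | 1.18 | 0.018 |
| m = 10, constant exposure, ICC 0.05 | 1.45 | 0.032 |
| m = 10, constant exposure, ICC 0.10 | 1.90 | 0.062 |

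With constant exposure and ICC 0.05, coverage of the 95% interval is 92.6% at m = 5 and 89.6% at m = 10. Power at 81 per group, without the continuity correction, is 84.8% under independence, 76.0% at DE 1.20 and 65.5% at DE 1.45.

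**5. Simulation of the ordinary Wald test.** Settings: 81 per group, FAI 27.5% in both groups, beta-binomial clusters, nominal 0.01. With independent data the test rejects in 0.008 of runs. At ICC 0.05:

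- Clubs of 5 in group 1 only: 0.011 to 0.012 (two separate simulations).
- Clubs of 10 in group 1 only: 0.017 to 0.019 (two separate simulations).
- Clusters of 10 in both groups, constant exposure: 0.031.
- A third to two-thirds of group 1 from clubs of 5 to 10: 0.009 to 0.014.
- Clusters split 75/25 and 25/75 by exposure: 0.011 at m = 5 and 0.013 at m = 10.

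**6. The remedy needs care.** With clubs of 10 in group 1 only, there are about 9 clubs and 81 single children, so roughly 90 clusters. The usual K/(K − 1) factor is then 90/89 = 1.01 and corrects almost nothing. A sandwich t-test with that factor still rejects in 0.0175 of null runs.

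**The case against.** A reader might infer that children are recruited in groups and that the reported interval and p-value are therefore too optimistic. The documents do not support that. No club, team or school is enrolled as a unit, schools only receive flyers, and consent is individual. With about 200 volunteers across several international sites, nothing shows how many will share a team.

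Nor is exposure constant within a club by design. Table 1 classifies each child from that child's own sport history, log and tracker. Groups are assigned only at the end of follow-up, and the sample size allows 10% for children who change group. A team-mate with a second sport falls in group 2. These points stand, and they pull the inflation towards the low end.

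A reader might also infer that power falls to about half. The simulated 51% belongs to the most clustered setting at ICC 0.05 (10 and 10, constant exposure) and to a K/(K − 1) robust test, not to the planned test. The closed form for the same setting gives 65.5%, and much of the gap reflects how that test behaves with few clusters.

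Finally, the variance estimator is commonly left to an SAP, and none is shown. That has force for the estimator alone. It does not cover the sample size, which the article states under independence. It also does not cover recruitment source: no later analysis can cluster on a source that was not captured. Table 3 lists enrolment data only as demographics, so whether the source is already recorded cannot be told.

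**Conclusion.** The point holds in conditional form. The model and the sample size both assume independence, while one recruitment route makes shared clubs plausible in the group where exposure would align with club. If several team-mates enrol, the standard error will be somewhat too small. At an assumed ICC of 0.05, the type I error at nominal 0.01 runs from about 0.010, through 0.011 to 0.019 when only group 1 is clustered in clubs of 5 to 10, to about 0.03 when both groups are in clusters of 10 with constant exposure. The last setting is an upper scenario for that ICC, since school flyers give little reason to expect group 2 clusters of that size with uniform exposure. ICC, cluster size and alignment of exposure with club are all assumptions. The logistic model and its odds ratio are not in error.

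**What to change.** - Record each participant's recruitment source at enrolment (club or team, school, or individual), and recover it from recruitment records for the 53 pilot participants.
- Keep the logistic model and its odds ratio. Report the confidence interval and p-value with cluster-robust variance, treating individually recruited children as clusters of one. Use a correction suited to few and unequal clusters, for example bias-reduced sandwich variance with Satterthwaite degrees of freedom. At minimum, pre-specify this as a sensitivity analysis.
- In Sample size calculation, state that the 80% power assumes independent children, and show power under a design effect once cluster sizes are known.

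The cost is one enrolment field, a retrospective check for the pilot and a short addition to the analysis text. The interval may be slightly wider and the stated power less favourable. No extra participants are needed, and if few children share a club the results will barely change.

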## Methods

### Study design

This is a longitudinal cohort study of 200 participants between the ages of 12 and 14 (i.e. critical age of development of the femoral head and neck). Participants will be evaluated clinically at enrollment and 6, 12, 18, and 24 months and radiographically (with MRI) at baseline and 24 months. Activity will be tracked every 3 months from enrollment to final follow-up at 2 years. Participants will be recruited from experienced hip surgeons and sports medicine researchers at multiple international clinical sites. We will observe the incidence of radiographic FAI, as determined by MRI of the hip, and evaluate hip function and HRQL using the HOS and PedsQL, respectively. Ethics approval for this study was granted by the Hamilton Integrated Research Ethics Board (Version D1.0, 1-August-2019, HIREB #7829). Any protocol amendments will be submitted to HIREB and communicated to all participating sites for submission their site-specific ethics boards.

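### The primary logistic model adjusts for BMI and sex but not for baseline age or physeal maturity, which the protocol itself treats as central to FAI

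*Protocol article*

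**What the plan says.** Under Primary analysis, the protocol article states that the model "will include the following independent variables: activity level (sport specialist versus non-sport specialist), body mass index (BMI), and sex". Under Subgroup/sensitivity analyses, the only addition is a sex-by-specialization interaction. No age, maturity or site term appears anywhere in the article.

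Other sections make maturity central to the question. Study design describes participants as "between the ages of 12 and 14 (i.e. critical age of development of the femoral head and neck". The Background says that open physes make children's hips more vulnerable. Study follow-up justifies the two-year duration by the expected timing of physeal closure. Eligibility criteria introduces the exclusions as mainly a means of removing known confounders, and lists first: "hip is mature (i.e. closed physes) based on the baseline MRI scan".

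The data are at hand. Age is an entry criterion ("asymptomatic males and females between the ages of 12–14 years") and Table 3 schedules "Enrolment data (Demographics". The baseline MRI is read for physeal status to decide eligibility, and Outcome measures says the study will document "the extent of physeal closure as these variables may predict future hip osteoarthritis". On site, Study design says: "Participants will be recruited from experienced hip surgeons and sports medicine researchers at multiple international clinical sites".

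**The concern.** Groups are formed by what participants do, so the odds ratio for specialization depends on how well the groups are made comparable. A child enrolled at 14 with a nearly closed physis and one enrolled at 12 with a wide-open physis pass through different parts of the window in which the protocol expects FAI to form. If specialists and non-specialists differ in baseline maturity, part of any difference in FAI may reflect maturity and not sport. The same difference could instead hide a real effect.

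The covariate list is written out in full, so this is a choice the document makes and not a detail left open for an analysis plan. Adding the term before the data are analysed is routine. Adding it afterwards would look data-driven.

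**Working it through.** **1. The plan's own figure.** Inputs (Sample size calculation): 40% versus 15%, two-sided alpha 0.01, power 80%. With mean proportion 0.275:

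n = [2.576 × √(2 × 0.275 × 0.725) + 0.842 × √(0.40 × 0.60 + 0.15 × 0.85)]² / 0.25² = 73.05, that is 74 per group.

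The continuity correction, n/4 × [1 + √(1 + 4/(n × 0.25))]², gives 80.85, that is 81 per group. This matches the plan, so the sample size is not in dispute here.

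**2. What an omitted age gradient could do.** The inputs are assumptions, because the document gives neither specialization nor FAI risk by age. Take ages 12, 13 and 14 in equal numbers, specialist shares s, FAI risks f, and no effect of specialization. Then

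P(FAI | specialist) = Σ(s × f)/Σs and P(FAI | non-specialist) = Σ((1−s) × f)/Σ(1−s).

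| Assumed s | Assumed f | Specialist | Non-specialist | Spurious OR |
|---|---|---|---|---|
| 35/50/65% | 12/25/40% | 0.427/1.5 = 0.285 | 0.343/1.5 = 0.229 | 1.34 |
| 40/50/60% | 15/25/35% | 0.395/1.5 = 0.263 | 0.355/1.5 = 0.237 | 1.15 |
| 35/50/65% | 40/25/12% | 0.229 | 0.285 | 0.74 |
| 40/50/60% | 35/25/15% | 0.237 | 0.263 | 0.87 |

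The last two rows reverse the risk gradient. The Background's statement that open physes are more vulnerable makes that direction at least as arguable.

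**3. Scale against the design.** The planned effect is (0.40/0.60)/(0.15/0.85) = 3.78. On the log scale the assumed biases are ln 1.34/ln 3.78 = 22% and ln 1.15/ln 3.78 = 11% of it. With no true effect and 81 per group, a normal approximation puts the two-sided rejection probability at about 4% (stronger gradient) or 1.6% (milder), against a nominal 1%.

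**4. Can the model carry another term?** Expected events are 81 × 0.40 + 81 × 0.15 = 44.6.

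- Planned three terms: 44.6/3 = 14.9 events per term.
- With age or baseline maturity, four terms: 44.6/4 = 11.1.
- Eight terms, as several site indicators could require: 44.6/8 = 5.6.

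**5. Cost in power.** If the added covariate explains a share R² of exposure, the effective size is about 81 × (1 − R²) per group. Without continuity correction:

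| R² | Effective n per group | Power | n needed to restore 81 |
|---|---|---|---|
| 0 | 81 | 84.8% | 81 |
| 0.05 | 77.0 | 82.5% | 81/0.95, so 86 |
| 0.10 | 72.9 | 79.9% | 81/0.90 = 90 |

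The R² values are assumptions.

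**The case against.** The best defence is that maturity is already controlled by design. Closed physes are excluded on the baseline MRI, age is limited to three years, and Table 1 writes a prepubertal condition into the criteria of both groups. That stands in part: restriction narrows the variation. It does not remove it, because every stage short of closure remains eligible.

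A reader might go further than the documents allow in three ways.

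- **That the odds ratio is biased.** Confounding needs a link with exposure as well as outcome. Nothing in the article says specialization becomes more common between 12 and 14. Table 1 does not supply the link, because its prepubertal condition applies to both groups. The statement about documenting physeal closure refers to future osteoarthritis, not to FAI.
- **That covariate adjustment is the only protection against confounding.** The exclusions are a stated, partial protection.
- **That leaving out site is an equal fault.** Recruitment through local schools, coaches and clubs may well make the share of specialists differ by site. But the number of sites is not given and no site effect can be quantified. Outcome measurement is protected by one specified MRI sequence, fixed criteria in Table 2 and adjudication blinded to activity level. The documents do not show that ignoring site distorts the standard errors, or in which direction.

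Parsimony is also a fair argument with about 45 events. It counts against many site indicators, but not against one maturity term.

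**Conclusion.** The point holds in a limited form. In a non-randomised comparison, the primary model omits a baseline variable that the protocol regards as central to the outcome, controls only by restriction, and already collects. Residual variation in maturity may bias the odds ratio if it is related to specialization.

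The spurious odds ratios of 1.15 to 1.34, or 0.74 to 0.87 with the gradient reversed, rest wholly on assumed gradients; they illustrate and do not estimate. They are modest beside the planned odds ratio of 3.78, so the omission would not by itself manufacture an effect of that size. It matters more if the true effect is small or absent. That age is recorded for everyone is inferred from the eligibility rule and the demographics form; physeal status on the baseline MRI is explicit. Site is a secondary matter and belongs in a sensitivity analysis.

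**What to change.** Add one prespecified covariate to the primary model: baseline age or baseline MRI physeal status. Name which one, and its form, before analysis. Do not use physeal closure at 24 months, which follows exposure and may lie on the causal path. Keep the model with BMI and sex only as a sensitivity analysis.

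In a separate sensitivity analysis, account for site by a random intercept, stratification or GEE, and not by a long set of indicators.

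The change needs plan wording only and no new data. Its price is the fall in events per term and the small possible loss of power worked out above.
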